### Data Collection and Management

Table 3 presents the detailed schedule for data collection and assessments. Baseline demographic and clinical data will be extracted from the hospital information system. Additional data—including mHealth use, electronic health literacy, EQ-5D-5L, and VTE-KAP—will be collected at discharge and follow-up via web-based questionnaires for the routine group and through the mVTEA platform for the intervention group. The Chinese version of the electronic health literacy scale (C-eHEALS) will be used to evaluate participants’ eHealth literacy [62]. Follow-up at 3 months postdischarge will be conducted through outpatient visits, telephone interviews, or web-based interviews via the mVTEA platform (for the intervention group). All collected data will be deidentified and recorded in electronic case report forms. Data will be securely stored on password-protected servers with restricted access, and sharing with third parties will require authorization from the corresponding author. The quality control team will routinely verify data accuracy and reliability; upon confirmation, the data will be locked to prevent further modifications. The finalized database will be provided to statistical analysts as specified in the statistical analysis plan. All data collectors and managers will undergo standardized training and assessment before participating in the study.

**Table 3 table3:** Study protocol, schedule, and timing of data collection.

Activity or assessment	Screening (during hospitalization, t_1_)	Enrollment (at discharge, 0)	Study visit (at discharge [intervention], t_1_)	Follow-up (3rd month, t_2_)
Prescreening consent	✓			
Eligibility screen	✓			
Informed consent		✓		
Randomization		✓		
Demographic information		✓		
Medical history		✓		
mHealth use		✓		
C-eHEALS^a^		✓		
VTE^b^-KAP^c^ questionnaire		✓		✓
EQ-5D-5L		✓		✓
Interventions				
Basic health education			✓	
mVTEA^d^-assisted management			✓	✓
Routine management			✓	✓
VTE event				✓
CTEPH^e^				✓
CTEPD^f^				✓
PPES^g^				✓
Bleeding event				✓
VTE-related hospitalization				✓
VTE-related rehospitalization				✓
Death				✓
New-onset of AFI^h^ or AFL^i^				✓
Adverse event				✓

^a^C-eHEALS: Chinese version of the electronic health literacy scale.

^b^VTE: venous thromboembolism.

^c^KAP: knowledge, attitude, and practice.

^d^mVTEA: smart technique-assisted patient-centered care mHealth app for managing venous thromboembolism.

^e^CTEPH: chronic thromboembolic pulmonary hypertension.

^f^CTEPD: chronic thromboembolic pulmonary disease.

^g^PPES: postpulmonary embolism syndrome.

^h^AFI: atrial fibrillation.

^i^AFL: atrial flutter.

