### Blinding

Due to the limitations of the protocol and the specific nature of mHealth management, it is not feasible to blind participants, their primary care physicians, and clinic physicians. However, to enhance the quality and reliability of this study, the researchers will be blinded during the efficacy assessment, data collection, data management, and statistical analysis of the results. Therefore, those responsible for efficacy assessment, data collection and management, and analysis of results will not be informed of trial group assignments and will not be permitted to communicate with each other or with participants about the treatment. Furthermore, to minimize potential bias introduced by unblinded participants or researchers, the study will include only individuals who have no conflict of interest.

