These VTE-KAP assessment outcomes determine the subsequent interventions delivered via the mVTEA app. Initially, upon registration, the mVTEA app delivers a standardized VTE education package containing 3 videos and 4 graphic resources covering VTE fundamentals, risk factors, symptoms, and prevention and treatment strategies. Following this initial phase, interventions are personalized based on the individual’s VTE-KAP scores. Tailored components include specific education schedules (basic or intensive), medication reminders, adherence feedback, risk monitoring features, access to electronic health records, and specialist communication channels. In addition, the mVTEA patient terminal automatically dispatches all health education questionnaires and home-rehabilitation reports according to the schedule specified in Table 2. The detailed workflow of this mVTEA-facilitated patient-centered VTE management strategy is presented in Figure 2, and the core functional interface of the mVTEA app is shown in Figure 3.

**Table 2 table2:** Distribution schedule of home rehabilitation reports and health education questionnaires for mHealth app-assisted, patient-centered venous thromboembolism management.

Timepoint	At discharge	1st month	2nd month	3rd month	6th month	9th month	12th month	>1 year
Home rehabilitation reports	None	✓	✓	✓	Once a month	Once a month	Once a month	Once a month
Knowledge questionnaire	✓	None	None	✓	✓	None	✓	Once every 6 months
Attitude questionnaire	✓	✓	✓	✓	✓	✓	✓	Once every 6 months
Practice questionnaire	✓	None	None	✓	✓	None	✓	Once every 6 months

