#### Routine VTE Management

The routine VTE management group will receive only conventional postdischarge management according to local clinical practice, including basic health advice appropriate for the prevention and treatment of VTE. The textual and graphical materials comprising the aforementioned basic package for VTE-related health education in the mVTEA app will be printed and distributed to patients within the routine management group on the day of discharge for home-based study. The video courses in the health education basic package can be accessed by scanning the QR code.

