#### Statistical Analyses

In this study, we define 2 analysis populations: full analysis set (FAS) and intention-to-treat (ITT). FAS is the set of all patients who have received VTE prevention and treatment intervention at least once after randomization. The ITT set will include all randomly assigned patients, regardless of whether they completed the study or followed the study protocol. FAS will be the primary analysis population, and ITT will provide supportive results. Missing data will be handled using the multiple imputation method. Since the study outcomes already include assessments of safety data, the safety analysis set is not performed. Sensitivity analysis will be conducted by comparing the results of the ITT and FAS analyses.

Continuous variables will be presented as mean and SD, or as median and IQR for variables not following a normal distribution. Categorical variables will be presented as counts and percentages. Differences in baseline demographic and clinical characteristics, as well as survey data between groups, will be assessed using the Student *t* test or the Mann-Whitney *U* test for continuous variables, depending on distributional assumptions. Categorical variables will be analyzed using the chi-square test or Fisher exact test, as applicable.

To account for the repeated measurements of EQ-5D-5L and KAP survey data collected at discharge and the 3-month follow-up, we will use a linear mixed-effects model for repeated measures. The model will include fixed effects for the treatment group (mVTEA management vs routine management), time point (discharge vs 3-month follow-up), the interaction between treatment group and time point, the baseline score of the respective survey (EQ-5D-5L or KAP), and the prestratification factors (VTE diagnosis status at discharge: Yes or No; age: ≥60 years vs <60 years). Patients and their hospitalization units will be included as random effects. The key parameter of interest for evaluating the intervention effect over time will be the group-by-time interaction term. The Cox proportional hazards model will be used to compare the hazard of the event (time to event) between groups during the follow-up period, taking into account the prestratification factors. The hazard ratio and its corresponding 95% CI will be calculated using this model. Statistical significance is set at *P*<.05 (2-sided). SPSS (version 22.0; IBM Corp) will be used for statistical analysis.

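### The discharge (baseline) VTE-KAP and EQ-5D-5L are collected through a different channel in each arm, so nothing ensures that they precede allocation or app content, although the key parameter subtracts them

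*Protocol article*

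**What the plan says.** Data Collection and Management says that mHealth use, eHealth literacy, EQ-5D-5L and VTE-KAP "will be collected at discharge and follow-up via web-based questionnaires for the routine group and through the mVTEA platform for the intervention group". The section on mVTEA-facilitated management agrees with this for KAP. It has the app's patient terminal send out the questionnaires on the Table 2 schedule, and Table 2 ticks knowledge, attitude and practice at discharge.

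On app content, the same section says: "Initially, upon registration, the mVTEA app delivers a standardized VTE education package containing 3 videos and 4 graphic resources". It continues: "Following this initial phase, interventions are personalized based on the individual’s VTE-KAP scores". It also says: "These VTE-KAP assessment outcomes determine the subsequent interventions delivered via the mVTEA app". Under Routine VTE Management, control patients receive the text and graphics of the same basic package, which "will be printed and distributed to patients within the routine management group on the day of discharge for home-based study"; the videos are reached by QR code.

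Table 3 ticks randomization, VTE-KAP and EQ-5D-5L in one enrollment column, with randomization in the higher row. Basic health education and both forms of management first appear in the next column, also at discharge.

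The Blinding section says that "it is not feasible to blind participants, their primary care physicians, and clinic physicians", and the VTE-KAP is self-administered. Statistical Analyses treats discharge as an outcome time point, also enters the baseline score as a fixed effect, and names the group-by-time interaction as the key parameter. The primary outcome is the between-group difference in KAP at 3 months.

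**The concern.** A baseline protects a randomized comparison only if allocation cannot have influenced it. Here three things could move the discharge score in one arm and not the other:

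- **Mode:** app versus web form.
- **Knowledge of the arm:** patients rate themselves after learning what they will receive.
- **Early content:** app-arm patients have to be on the platform to answer, and registration releases education material.

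The first two follow from the text as written. The third is possible but not established. It is plausible mainly for the knowledge and attitude domains of the KAP. For EQ-5D-5L, only mode and knowledge of allocation apply.

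The discharge score enters the named effect parameter directly. With two time points, the interaction is the difference between arms in change from discharge to month 3. A shift at discharge in one arm therefore passes into the reported effect in full, with the opposite sign.

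**Working it through.** **Inputs from the protocol (Sample Size and Power Considerations):** 100 evaluable patients per group, coefficient of variation 0.1 (SD = 10% of the mean score), target difference 5% of the mean, two-sided alpha 0.05.

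**Assumed, because the protocol gives neither:** a correlation r between discharge and month-3 scores of 0.3, 0.5 or 0.7, and an app-arm baseline shift c of 0 to 3% of the mean score.

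**Step 1, the plan's own figure.** SE = 10% × √(2/100) = 1.414%. Then 5/1.414 = 3.536, and power = Φ(3.536 − 1.960) = 94.2%. At alpha 0.025 it is 90.2%. The stated 94% and 90% are reproduced. This calculation describes a plain two-group comparison of scores, without a baseline.

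**Step 2, what a shift does to the interaction.** Expected estimate = 5% − c. SE = 10% × √(2(1 − r)) × √(2/100). At r = 0.5 the SE is again 1.414%:

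- c = 1%: 4/1.414 = 2.828; power = Φ(0.868) = 80.7%
- c = 2%: 3/1.414 = 2.121; power = Φ(0.161) = 56.4%

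| Shift c | Interaction estimates | Power, r = 0.3 | Power, r = 0.5 | Power, r = 0.7 |
|---|---|---|---|---|
| 0 | 5% | 84.8% | 94.2% | 99.5% |
| 1% | 4% | 66.7% | 80.7% | 95.5% |
| 2% | 3% | 43.4% | 56.4% | 78.2% |
| 3% | 2% | 22.2% | 29.3% | 44.7% |

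A simulation at r = 0.5 and c = 2% gave an interaction estimate of 3.0%, as the formula predicts. Adding the baseline score as a covariate does not help: with complete data, a covariate that is constant over time leaves the interaction unchanged.

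**Step 3, no true effect.** At r = 0.5, a shift of 1% or 2% in either direction gives two-sided rejection in 11% or 29% of trials instead of 5%. An app-arm baseline that is too high produces false findings in favour of routine care. A false benefit of the app needs a baseline that is too low.

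**Step 4, other analyses.** A month-3 comparison adjusted for the baseline score estimates 5% − r × c. At r = 0.5 this is 4.5% for c = 1% (power 95.7%) and 4.0% for c = 2% (power 90.4%). A month-3 comparison that does not use the survey baseline is unaffected by c and keeps 94.2%. If both arms shift by the same amount, the bias is zero in every analysis.

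**The case against.** A reader might infer that the baseline is a post-treatment measure and that the primary result is therefore biased. The documents do not support that. Table 3 puts both questionnaires one column before education and app management. The intervention text says that KAP results determine what is delivered next, which also points to questionnaire first. Nowhere is it said that app content is viewed before the first KAP, and material that has been delivered has not necessarily been watched. Figures 2 and 4, which I have not seen, may show the order.

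The sentence on collection channels is also a loose summary. It applies discharge and follow-up to mHealth use and eHealth literacy as well, whereas Table 3 ticks these at enrollment only. Control patients get the same basic material on the same day, so exposure might be similar in both arms and cancel. The size and sign of any shift are assumed. Nor is a missing baseline peculiar to the app arm: a routine patient can leave the web form unanswered. Finally, the primary outcome is defined as the month-3 difference, and the planned simple tests on survey data arguably include such a comparison.

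Most of this stands, and it limits the point to a safeguard that is missing. It does not remove it. The arm-specific channel is stated, and the dispatch of the discharge KAP by the app supports it independently. Table 3 separates the surveys from education but does not place them before randomization. The simple tests are not named as the primary analysis, whereas the interaction is named as the key parameter.

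**Conclusion.** The concern holds as a weakness in sequence and mode. As written, discharge VTE-KAP and EQ-5D-5L are completed after allocation is known, by unblinded patients, through different channels. In the app arm this happens on the platform that releases education at registration. Whether any content is seen first is left open, so the intervention section, Data Collection and Management, and Tables 2 and 3 need to be reconciled.

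The effect on the interaction is exact in form: a shift in one arm is subtracted one-for-one. Its size and direction are unknown. Because the target is only 5% of the mean score, small shifts would matter. Under the assumed correlation of 0.5, a rise of 1% or 2% in the app arm takes power from 94% to 81% or 56%; over correlations of 0.3 to 0.7, power at 2% runs from 43% to 78%. These figures illustrate the risk and do not estimate an actual bias.

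**What to change.** **Procedure, for all remaining patients.** VTE-KAP, EQ-5D-5L, C-eHEALS and mHealth use are completed on the one existing web form, after consent and before randomization. App registration and all education material, in both arms, come afterwards. The app uses that score for tailoring. Amend the sections and tables named above to show this order.

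**Patients already enrolled (185 at submission).** Where time stamps exist, flag baselines taken after allocation or after app content. At most 256 − 185 = 71 patients could benefit from the new order as of submission, so the change to the analysis matters more.

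**Analysis.** Before the database is locked and unblinded, prespecify a month-3 KAP comparison adjusted for the stratification factors only, which matches the stated primary outcome. State then whether it is the primary or the sensitivity analysis. Its rank must not depend on whether it disagrees with the mixed model.

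**Cost.** A few minutes of questionnaires before randomization, with no added patients. Leaving out the baseline costs some precision: at correlation 0.5 and with a valid baseline, a baseline-adjusted month-3 comparison would have 98.3% power, against 94.2% without the covariate. The trial would also contain two kinds of baseline, to be reported by period.

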### Quality Control

To ensure the quality of the study, all researchers will undergo uniform and standardized training before the study’s commencement. Researchers will be assessed, and only those who meet the qualifications will be allowed to participate. Structured follow-ups will be conducted by staff from the specialized follow-up office. In addition, the collected data will be regularly monitored monthly by the research supervisor to ensure the authenticity and reliability of the study results.

### Statistics

#### Sample Size and Power Considerations

This study used a stratified block randomization method with 4 strata. Literature suggests an average of 50-100 patients per stratum for stratified randomization [63]. Previous studies in China have reported that the coefficient of variation for VTE-KAP questionnaire scores among patients at risk of VTE ranges from 0.1 to 0.12. In this study, a coefficient of variation of 0.1 was assumed, enrolling 50 patients per stratum, resulting in a total of 200 patients (100 per group). At a 2-sided significance level of .05, this design yields 94% statistical power to detect a 5% difference in VTE-KAP questionnaire scores between the two groups. Even with a 2-sided significance level of 0.025, the setup maintains 90% statistical power to detect the same 5% difference. Considering a 20% nonresponse rate, the final sample size was adjusted to 64 patients per stratum, leading to a total of 256 patients (128 in each group). The sample size was calculated by using Power Analysis and Sample Size software (version 19.4.1; NCSS, LLC).

#### Statistical Analyses

In this study, we define 2 analysis populations: full analysis set (FAS) and intention-to-treat (ITT). FAS is the set of all patients who have received VTE prevention and treatment intervention at least once after randomization. The ITT set will include all randomly assigned patients, regardless of whether they completed the study or followed the study protocol. FAS will be the primary analysis population, and ITT will provide supportive results. Missing data will be handled using the multiple imputation method. Since the study outcomes already include assessments of safety data, the safety analysis set is not performed. Sensitivity analysis will be conducted by comparing the results of the ITT and FAS analyses.

Continuous variables will be presented as mean and SD, or as median and IQR for variables not following a normal distribution. Categorical variables will be presented as counts and percentages. Differences in baseline demographic and clinical characteristics, as well as survey data between groups, will be assessed using the Student *t* test or the Mann-Whitney *U* test for continuous variables, depending on distributional assumptions. Categorical variables will be analyzed using the chi-square test or Fisher exact test, as applicable.

To account for the repeated measurements of EQ-5D-5L and KAP survey data collected at discharge and the 3-month follow-up, we will use a linear mixed-effects model for repeated measures. The model will include fixed effects for the treatment group (mVTEA management vs routine management), time point (discharge vs 3-month follow-up), the interaction between treatment group and time point, the baseline score of the respective survey (EQ-5D-5L or KAP), and the prestratification factors (VTE diagnosis status at discharge: Yes or No; age: ≥60 years vs <60 years). Patients and their hospitalization units will be included as random effects. The key parameter of interest for evaluating the intervention effect over time will be the group-by-time interaction term. The Cox proportional hazards model will be used to compare the hazard of the event (time to event) between groups during the follow-up period, taking into account the prestratification factors. The hazard ratio and its corresponding 95% CI will be calculated using this model. Statistical significance is set at *P*<.05 (2-sided). SPSS (version 22.0; IBM Corp) will be used for statistical analysis.

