## Methods

### Study Design and Setting

The SmaVTE study is a 2-armed, single-center, parallel-group, randomized controlled trial designed to evaluate the impact of the mVTEA app on the KAP of patients with or at high risk of VTE. The trial will be conducted at the Sixth Medical Center of the Chinese People’s Liberation Army General Hospital, which is a tertiary hospital that integrates medical care, teaching, and research. A total of 256 hospitalized patients with or at high risk of VTE will be recruited on the day of their discharge. Participants will be randomly allocated in a 1:1 ratio to either the mVTEA management group or the routine management group. The mVTEA management group (n=128), also referred to as the experimental group, will receive patient-centered VTE management facilitated by the mVTEA app after discharge. In contrast, the routine management group (n=128), also known as the control group, will be administered with conventional postdischarge management according to local clinical practice. All of the above management will be performed for 3 months following discharge. Our study is scheduled to commence in August 2024 and conclude in November 2025. Recruitment began in August 2024 and is anticipated to conclude by June 2025. Data analysis is planned to commence in October 2025 after the follow-up data collection. The analysis is expected to be completed by November 2025. The protocol conforms to the SPIRIT (Standard Protocol Items: Recommendations for Interventional Trials) 2013 statement [37]. The latest protocol (version 1.0) was dated March 1, 2024. The trial was registered on Clinicaltrials.gov (NCT06350331).

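### The primary analysis set depends on receiving the intervention after randomization, with ITT only supportive, so randomized non-starters can leave the primary comparison

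*Protocol article*

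**What the plan says.** The Statistical Analyses section of the protocol article defines two populations and ranks them.

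- FAS: "FAS is the set of all patients who have received VTE prevention and treatment intervention at least once after randomization".
- ITT: "The ITT set will include all randomly assigned patients, regardless of whether they completed the study or followed the study protocol".
- Ranking: "FAS will be the primary analysis population, and ITT will provide supportive results".

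The planned sensitivity analysis is a comparison of the two sets. On incomplete data the section says: "Missing data will be handled using the multiple imputation method". The key parameter for KAP and EQ-5D-5L is the group-by-time interaction in a mixed model that also contains the baseline score. Events are compared with a Cox model.

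The arms differ in how the intervention first reaches the patient. In the app arm, "upon registration, the mVTEA app delivers a standardized VTE education package" (mVTEA-Facilitated Patient-Centered VTE Management). In the control arm, the text and graphics of the same basic package "will be printed and distributed to patients within the routine management group on the day of discharge for home-based study" (Routine VTE Management). Allocation is known to patients and their physicians: "it is not feasible to blind participants, their primary care physicians, and clinic physicians" (Blinding).

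**The concern.** Randomization protects a comparison of everyone who was allocated. Once membership of the primary set depends on something that happens after allocation, that protection holds only if the act is unrelated to outcome or equally selective in both arms. Here patients know their arm, and the route to first receipt is not the same: registration on an app in one arm, a handout from staff in the other. Patients who never start the app may be less engaged or less comfortable with digital tools. The article itself notes that mHealth engagement wanes (Introduction) and that digital literacy is a potential source of bias (Limitations). Both plausibly relate to a self-administered KAP score.

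The stake is the trial's headline answer. The objective is to learn whether the app improves KAP compared with usual management, and failure to take up the app is part of that effect. If FAS and ITT disagree, the plan as written lets the FAS result stand as the primary one.

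**Working it through.** **Plan's own figures (Sample Size and Power Considerations).** Inputs: coefficient of variation 0.1, difference 5% of the mean, 100 per group, 20% nonresponse.

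- Standardized effect: 5% / 10% = 0.5 SD, where SD means the SD of the KAP score (10% of the mean) throughout.
- SE of the difference: 0.1 x sqrt(2/100) = 0.01414, and 0.05 / 0.01414 = 3.54.
- Power at two-sided 0.05: 94.2% (noncentral t: 94.0%). At two-sided 0.025: 90.2% (t: 89.8%). The stated 94% and 90% reproduce.
- Size: 50 / 0.8 = 62.5 per stratum, so 63, rounded to 64 for blocks of 4; 64 x 4 = 256. This reproduces.

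**Bias from excluding non-starters.** Let p be the share of the app arm that never starts, and let m_S and m_N be the mean 3-month changes of starters and non-starters.

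- All-randomized app mean: (1 - p) m_S + p m_N.
- FAS app mean: m_S.
- Difference: p (m_S - m_N) = p x delta, where delta is the non-starters' deficit in change.

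The deficit must be in change because the model targets the group-by-time interaction. A deficit in level that is fully present at discharge cancels. If half of a 0.5 SD deficit at 3 months is already there at discharge, delta is 0.25 SD. If controls are excluded too, their own p x delta is subtracted.

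The documents give neither p nor delta. With assumed p = 5-15% and delta = 0.5-1.0 SD, and exclusions in the app arm only:

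- Low: 0.05 x 0.5 = 0.025 SD, which is 0.025 / 0.5 = 5% of the planned effect.
- High: 0.15 x 1.0 = 0.15 SD, which is 0.15 / 0.5 = 30% of the planned effect.

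**Effect on type I error.** This is an illustration: no true effect, a two-sample comparison with SD 10% of the mean, and 100 per arm before exclusions from the app arm only. It does not model the planned mixed model.

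| p | delta | Type I error |
|---|---|---|
| 5% | 0.25 SD | 5.1% |
| 10% | 0.5 SD | 6.4% |
| 10% | 1.0 SD | 10.6% |
| 15% | 1.0 SD | 17.4% |

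**Power with ITT primary.** If non-starters gain nothing, the effect is diluted to 5% x (1 - p).

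| p | Power, 100 per arm | Power, 128 per arm |
|---|---|---|
| 0% | 94.2% | 97.9% |
| 5% | 91.9% | 96.7% |
| 10% | 88.9% | 95.0% |
| 15% | 85.2% | 92.5% |
| 20% | 80.7% | 89.3% |

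**Limit of imputation.** If non-starters have no 3-month KAP and their change is imputed from app-arm starters, the ITT mean becomes (1 - p) m_S + p m_S = m_S. That is the FAS answer again. Relabelling the primary set therefore helps only as far as non-starters are actually followed up.

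**The case against.** A reader might infer that app patients have to register and use the app after leaving hospital, so that non-starters will be dropped from that arm while practically every control qualifies. The documents do not support this.

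- Data Collection and Management has the intervention group's discharge questionnaires collected through the mVTEA platform.
- Table 2 dispatches the knowledge, attitude and practice questionnaires at discharge.
- Table 3 ticks both basic health education and mVTEA-assisted management at the discharge intervention visit.
- The FAS asks for receipt, not use.

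On that schedule first receipt can be a discharge-day event in both arms, with little time to drop out beforehand. Patients unable to use smart devices are excluded before randomization. The FAS is not a completer set, since patients who start and later disengage stay in. ITT is also reported, so a material discrepancy would be visible. A reader might also take 5-30% of the planned effect as an estimate of the bias; it rests wholly on assumed inputs.

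Most of this stands as a limit on size and direction. It does not settle the matter. The article does not say what counts as having received the intervention in either arm, and first app content is tied to a step that controls do not face. If exclusions are few, making ITT primary costs almost nothing. If they are many, a FAS-primary result is hard to defend. Reporting ITT as supportive does not change which result is the trial's answer.

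**Conclusion.** The point holds as a wrong choice of primary set. The article states the ranking outright, so it is not a detail left to a separate analysis plan. Randomized patients who never start can leave the primary comparison of an open-label superiority trial. That the loss falls more on the app arm, and so favors it, is plausible but inferred, and the schedule suggests that exclusions may be few. For an assumed non-start share of 5-15% and a deficit in change of 0.5-1.0 SD, with exclusions only in the app arm, the bias is 0.025-0.15 SD. It is smaller to the extent that the deficit is already present at baseline, and near zero if discharge-day education counts as receipt for nearly everyone.

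**What to change.** In the Statistical Analyses section:

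1. Make ITT (all randomized patients, analyzed as allocated) the primary population for KAP, EQ-5D-5L and the event outcomes, and make FAS supportive.
2. State what counts as first receipt in each arm, so that the FAS is reproducible.
3. Seek 3-month KAP from patients who never start, through the outpatient and telephone routes already planned in Data Collection and Management. Use the planned multiple imputation only for what is still missing.
4. Document the change before unblinding.

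Cost: a few sentences and some follow-up effort. Both sets are already planned and the sample size stays at 256. The estimate may be smaller, and power is somewhat lower if non-starters gain no benefit: at 100 per arm, about 94% falls to 89% with 10% non-start.

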### Outcome Measures

#### Primary Outcome

The primary outcome of this study is the difference in patients’ KAP on VTE at 3-month follow-up between the mVTEA management group and the routine management group.

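### Read literally, the 3-month KAP score falls under both an unadjusted two-sample test and a mixed-model interaction at P<.05, and neither is named as the deciding primary analysis

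*Protocol article*

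**What the plan says.** Four statements in the protocol article bear on how the primary endpoint is tested.

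- **Primary Outcome:** "The primary outcome of this study is the difference in patients’ KAP on VTE at 3-month follow-up" between the two groups.
- **Sample Size and Power Considerations:** "a coefficient of variation of 0.1 was assumed, enrolling 50 patients per stratum, resulting in a total of 200 patients (100 per group"). From these inputs, "At a 2-sided significance level of .05, this design yields 94% statistical power to detect a 5% difference in VTE-KAP questionnaire scores" between the groups. No baseline to follow-up correlation enters.
- **Statistical Analyses, second paragraph:** group differences in baseline characteristics, "as well as survey data between groups, will be assessed using the Student" t test or the Mann-Whitney U test, chosen by distribution. No time point is given for the survey data.
- **Statistical Analyses, third paragraph:** for EQ-5D-5L and KAP at discharge and 3 months, "we will use a linear mixed-effects model for repeated measures", with baseline score and both stratification factors among the fixed effects. Then: "The key parameter of interest for evaluating the intervention effect over time will be the group-by-time interaction term".

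One threshold covers everything: "Statistical significance is set at *P*<.05 (2-sided"). In this section the word primary is attached to an analysis population, not to a test.

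**The concern.** The outcome definition and the sample size fit a two-sample comparison of 3-month scores. The sentence on the key parameter points to a difference in change from discharge. Under randomization both estimate the same expected effect, but they are different statistics with different precision, and in a given trial they can fall on opposite sides of .05.

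Two things are at stake. If the report could rest on whichever result is significant, the 5% error rate would not hold. And if the two results differ, the article gives no explicit rule for which one answers the primary question. In addition, the stated 94% power belongs to the two-sample test and does not carry over automatically to the interaction.

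**Working it through.** **Inputs from the article:** 100 per group; SD 10% of the mean (coefficient of variation 0.1); difference 5% of the mean; two-sided .05.

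**Assumption:** correlation r between discharge and 3-month KAP of 0.3, 0.5 or 0.7, with equal variances at both times. The article gives no value.

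**Step 1. Reproduce the stated power.** The expected z for a two-sample comparison is (5/10) × √(100/2) = 3.536. Power is Φ(3.536 − 1.960) = 94.2%, or 94.0% with the t distribution. At .025 it is 90.2% (z) or 89.8% (t). The article's 94% and 90% are therefore those of an unadjusted two-sample test.

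**Step 2. Expected z for the other contrasts.**

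- Interaction, treated as a difference in change between two time points: 3.536 / √(2(1 − r)).
- 3-month difference adjusted for baseline as a covariate: 3.536 / √(1 − r²).

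**Step 3. Joint behaviour of the two planned tests.** The correlation between the 3-month contrast and the change contrast is √((1 − r)/2), which is 0.592, 0.500 and 0.387 for the three values of r. The bivariate normal distribution then gives:

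| | r = 0.3 | r = 0.5 | r = 0.7 |
|---|---|---|---|
| No effect: either test P<.05 | 8.8% | 9.1% | 9.4% |
| 5% difference: tests disagree on significance | 14.4% | 8.5% | 5.9% |
| 2.5% difference: tests disagree | 29% | 33% | 40% |
| Power at 5%: two-sample test | 94.2% | 94.2% | 94.2% |
| Power at 5%: interaction | 84.8% | 94.2% | 99.5% |
| Power at 5%: baseline-adjusted 3-month difference | 96.0% | 98.3% | 99.9% |

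**Step 4. Check by simulation.** With normal data, no effect and 20,000 trials per setting, the chance that either the t test or the change test is significant was 8.75%, 8.82% and 9.22% at 100 per arm, and 8.98%, 8.97% and 9.41% at 128 per arm. Two independent tests would give 1 − 0.95² = 9.75%. Each test used alone stayed at about 5% (4.7% to 5.3%).

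**Step 5. A milder reading of the model.** If the mixed model is taken as a baseline-adjusted 3-month comparison, its correlation with the unadjusted test is √(1 − r²), and the either-test figure falls to 6.4%, 7.3% and 8.3%.

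**The case against.** The strongest reply is that the plan already leans one way. Only the mixed model is tied to the intervention effect, through the key-parameter sentence, and nothing comparable is said of the t or U test. That stands: it would be wrong to say that the article gives no direction. But the sentence concerns the effect over time, does not call the interaction the primary analysis, and does not match the contrast that was defined and powered.

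Second, the t/U sentence opens with baseline characteristics. Data Collection and Management separates clinical data taken from the hospital system from questionnaire data collected at discharge and follow-up, so the survey data may mean the discharge questionnaires only. On that reading there is no second efficacy test. It is plausible, but the sentence does not say so, and the next paragraph uses the same term for both time points.

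Third, a reader might infer that the plan as written inflates the type I error. The article does not support this. Inflation needs a rule that either test suffices, and none is stated; with any one deciding test the error is about 5%. Nor are the t and U tests two chances: one is selected by distribution, and even taking the smaller of their P values gives only about 6%. EQ-5D-5L is a secondary outcome, so an overlap there does not touch the primary error rate.

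Fourth, ranking analyses can be left to a statistical analysis plan, which the article mentions and which is not shown. That plan may settle the matter. The point here is not an omitted detail, however: the analyses the article does state overlap on the primary endpoint, and the named parameter differs from the outcome as worded.

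**Conclusion.** The point holds as an ambiguity in the primary analysis with a possible, not a demonstrated, cost in type I error. Read literally, KAP is under two tests at the same threshold. The outcome and the power calculation fit one, and the key parameter fits the other.

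The size depends on use. It is about 9% false positives if either test could carry the claim, and 5% if one test decides. Independently of any selection, the tests disagree in about 6% to 14% of trials at the design effect, and in 29% to 40% at half of it. Power for the interaction could be anywhere from about 85% to 99.5%, so the stated 94% is not assured for it.

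These figures rest on the assumed correlation of 0.3 to 0.7, equal variances, approximate normality, complete data on 100 per group, and the interaction behaving as a difference in change.

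**What to change.** Make two wording changes in Statistical Analyses before unblinded analysis begins (data analysis is planned from October 2025).

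1. Limit the t test/Mann-Whitney sentence to baseline or descriptive comparisons, so that it no longer covers 3-month KAP.
2. Name one deciding primary analysis at two-sided .05: the between-arm difference in 3-month KAP total, adjusted for baseline KAP and the two stratification factors (age group and VTE diagnosis status). Baseline KAP should enter as a covariate only, not also as one of the outcome time points. Label any unadjusted comparison supportive.

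This matches the primary outcome as worded, keeps the error at 5%, and under the same assumptions has 96% to 99.9% power at the design effect, against 94% for the unadjusted test. The cost is wording only: discharge and 3-month KAP and both stratification factors are already collected, and the sample size does not change.
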